#### Recruitment

The three study centres engage in the recruitment of participants and physiotherapy practices by means of letter mailings, press releases, print media (flyers, posters), information events, newsletter, websites, an animated explanatory film and an article in the customer magazine of the health insurance company (Techniker Krankenkasse (TK)). In addition, a personalized mailing will be sent from the TK to eligible patients in the regions of interest. Cooperating physicians are asked to make their patients aware of the study. Patients interested in participating must contact their trial centre for a comprehensive informed interview addressing questions and study eligibility.

Patient recruitment will extend over 9 months (November 2022 to June 2023). An extension may be required, should the COVID-19 pandemic result in restrictions at cooperating institutions that cannot be controlled by the study centres. Figure 5 provides an overview of the entire recruitment process.

**Fig. 5 Fig5:**
[figure not shown]
Flow-Chart of the recruitment, screening, assessment and randomization process

#### Eligibility criteria

Patients with OA at the hip and/or knee joint diagnosed by a physician according to the criteria of the “American College of Rheumatology” [79, 80] are eligible for this trial. The minimum age for patients with hip and knee OA is 50 and 38 years, respectively. The responsible physician must verify the patient’s eligibility for inclusion in advance with the “Infozept” (green prescription). Additionally, participants need to be insured with TK, and have sufficient German language skills for the assessments and the intervention of at least B2 level according to the Common European Framework of Reference for Languages [81]. In addition, participants need internet access at home and a SIM card (see Table 5). A smartphone can be provided, if wanted.

**Table 5 Tab5:** Inclusion and exclusion criteria for study participation

Inclusion criteria	Exclusion criteria
• Physician-diagnosed OA of the hip and/or knee according to the clinical criteria of the American College of Rheumatology (ACR) [79, 80] ICD-10-GM: M15 polyarthrosis, M16 coxarthrosis; M17 gonarthrosis	• Patients with a fixed date for a replacement surgery of the affected joint or already having a total replacement of the affected joint
• Patients with hip OA aged > 50 years; patients with knee OA aged > 38 years according to the ACR [79, 80]	• Patients without internet access at home
• Medically eligible to participate in the SmArt-E intervention	• Inability to understand the German language (B2-level)
	• Patients who are not medically eligible to participate in the Smart-E intervention (e.g. contraindications like cardiovascular or neurological diseases)

#### Randomization and blinding

At t0 (initial assessment) the assessors will allocate participants to the intervention or control group by block randomization using REDCap (Vanderbilt University, Nashville, Tennessee, USA), for which a 1:1 allocation ratio stratified by the affected joint (hip vs. knee), sex, and study centre will be applied. Participants of the intervention group will be treated in the nearest participating physiotherapy practice.

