Key secondary outcomes	Three assessments are scheduled: 1. T0 assessment = following enrolment and before randomization/ start of the intervention; 2. T1 assessment = 3 months after the start of the intervention/ after completion of the in-person intervention; 3. T2 = after completion of the 12-months study period. 1. HOOS or KOOS and NRS after 3 months 2. Physical performance tests (modified Y-Balance Test; 30-second Sit-to-Stand Test) after 3 and 12 months 3. Daily physical activities (assessment is device-based and questionnaire-based) after 3 and 12 months Questionnaire surveys: 4. Action and coping planning (Action Planning & Coping Planning) at 3 and 12 months. 5. Quality of life/ health status (European Quality of Life 5 Dimensions 5 Level Version (EQ-5D-5L), Patient Global Assessment (PGA) and self-rated change in health status after 3 and 12 months 6. Assessment of coping strategies for pain and its evaluation (Pain Catastrophizing Scale, PCS) after 3 and 12 months 7. Self-report behavioural automaticity index (SRBAI) after 3 and 12 months 8. Assessment of the general improvement of the disease (Patient Acceptable Symptom Scale, PASS) after 3 and 12 months 9. Self-efficacy/ empowerment (Arthritis Self-Efficacy Scale, ASES) after 3 and 12 months 10. Patient satisfaction (ZUF-8) and an additional item assessing the patient’s perspective on the satisfaction with the results of the treatment after 3 and 12 months 11. Physical activity health competence (short form) after 12 months 12. Usability: System Usability Scale (SUS) after 3 months and mHealth App Usability Questionnaire (MAUQ) after 12 months 13. Questions on health care expenditures (financial expenditures due to osteoarthritis-related knee/hip problems for utilization of health care providers, therapeutic treatments, aids, etc.) for the period 12 months before study inclusion and during the 12-months intervention period

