### Outcomes (measures)

Table 4 shows descriptive variables, as well as primary and secondary outcomes. Assessors receive 2 h of training on all aspects of the assessment to ensure a high level of standardization.

**Table 4 Tab4:** Overview of outcome measures, screening instruments and descriptive measures over the course of the study

		PS	TS	T_**0**_	T_**1**_	T_**2**_
	*Sociodemographic and health-related data*					
	Date of birth, age, and sex			X		
	School-leaving qualification; academic grades; employment; living conditions (i.e., living alone/ in a nursing home); monthly net income;			X		
	German-speaking		X			
	*Medical and medication information*					
	Height; weight; body mass index; health status; co-morbidities; walking aids			X		
	OA-related treatment history and surgery; previous joint replacement			X		
	Screening for study eligibility and absence of contraindications	X	X			
	*Physical functioning*					
P	Hip Disability and Osteoarthritis Outcome Score (HOOS)			X	X	X
P	Knee injury and Osteoarthritis Outcome Score (KOOS)			X	X	X
	*Pain and tiredness*					
P	Numeric rating scale (NRS)			X	X	X
	*Physical capacity*					
S	Modified Y-Balance-Test			X	X	X
S	30-Second Chair Stand Test (30s CST)			X	X	X
	*Physical activity*					
S	ActiGraph 3 GT3X tri-axial accelerometers and activity diary			X	X	X
S	Activity questionnaire			X	X	X
	*Action planning and coping planning*			X	X	X
S	*Questionnaire*					
	*Health-related quality of life, health status*					
S	European Quality of Life 5 Dimensions 5 Level Version (EQ-5D-5L)			X	X	X
S	Patient Global Assessment (PGA)			X	X	X
S	Subjective change of health status				X	X
	*Coping strategies*					
S	Pain Catastrophizing Scale (PCS)			X	X	X
	*Psychosocial status*					
S	Self-Report Behavioral Automaticity Index (SRBAI)			X	X	X
S	Patient Acceptable Symptom State (PASS)			X	X	X
S	Arthritis Self-Efficacy Scale (ASES)			X	X	X
	*Satisfaction*					
S	ZUF-8 questionnaire + 1 item for patient perspective on satisfaction with treatment results				X	X
	*Usability*					
	System Usability Scale (SUS)				X	
	mHealth App Usability Questionnaire (MAUQ)					X
	*Health literacy*					
	European Health Literacy Survey (HLS-EU-Q16)			X		
	eHealth Literacy Scale (eHEALS)			X		
S	Movement-related Health Literacy			X		X
	*Technology readiness*					
	Technology commitment			X		
	*Health Economic Evaluation* Questions on out-of-pocket expenses and resource use			X		X

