##### Physical activity (PA)

Daily PA will be assessed using ActiGraph GT3X triaxial accelerometers [48], successfully used in previous clinical trials including patients with knee and/or hip OA [49]. Participants wear the accelerometer attached to a waist belt for ten consecutive days throughout their waking hours, except for showering or swimming. Additionally, participants will be asked to complete a short activity diary including wearing time, unusual activities, or activities difficult to detect, as well as reasons and duration for removal of the device. Data will be recorded at a sampling rate of 100 Hz. After returning the accelerometer and diary, data will be downloaded, processed, and analysed, for which the Freedson thresholds will be used. 0–99 counts per minute (CPM) indicate sedentary behaviour, while values between 100 and 1951, 1952–5724, 5725–9498, and values ≥9499 CPM indicate light, moderate, vigorous, and very vigorous PA, respectively [50]. Valid PA assessments require a minimum wear time of at least 7 days, 10 h per day [51].

Additionally, we will use a questionnaire on daily PA focusing on leisure and work, comprising nine items that are part of the “German Health Update” (GEDA) study of the Robert Koch Institute [52], and a single question derived from the Global Physical Activity Questionnaire developed by the WHO on daily sitting time [53].

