### Participants

#### Participant timeline

Study participation begins with an initial assessment (t0), followed by randomization of participants. The SmArt-E intervention expands over 12 months with follow-up assessments at 3 (t1) and 12 months (t2) after the start of the intervention and starting with in-person physiotherapy. A refresher session is held after 6 months (see Fig. 4).

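### Assessors carry out the randomisation themselves, so the staff group that runs the follow-up performance tests knows the arm, and the ten-day T0 accelerometry is not clearly placed before allocation

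*Protocol article*

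**What the plan says.** Under Randomization and blinding the protocol article states "At t0 (initial assessment) the assessors will allocate participants to the intervention or control group by block randomization using REDCap", with a "1:1 allocation ratio stratified by the affected joint (hip vs. knee), sex, and study centre will be applied". Despite its heading, that section says nothing about who is blinded.

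Under Outcomes (measures), "Assessors receive 2 h of training on all aspects of the assessment to ensure a high level of standardization". Table 4 in that section lists the modified Y-Balance Test and the 30-second chair stand test as secondary outcomes at T0, T1 and T2. The registration table (Table 1, Study design) lists among the key secondary outcomes "Physical performance tests (modified Y-Balance Test; 30-second Sit-to-Stand Test) after 3 and 12 months".

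On timing, Table 1 defines "T0 assessment = following enrolment and before randomization/ start of the intervention", and Participant timeline says "Study participation begins with an initial assessment (t0), followed by randomization of participants". Table 4 also marks "ActiGraph 3 GT3X tri-axial accelerometers and activity diary" as a T0, T1 and T2 measure. According to Physical activity (PA), "Participants wear the accelerometer attached to a waist belt for ten consecutive days throughout their waking hours", after which the device and diary are returned.

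**The concern.** Whoever operates the allocation sees the result. When that task belongs to the assessors, knowledge of the arm lies with the group that measures outcomes. Most outcomes here are questionnaires completed by participants who cannot be blinded to a training and app programme. The two performance tests are among the few outcomes that a blinded examiner could protect. Both depend on effort: reach distance in one, repetitions within 30 seconds in the other. Encouragement, the acceptance of an attempt and counting can all drift with the examiner's expectations.

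The second issue is the baseline for device-measured activity. The intervention aims to raise physical activity. If the baseline recording runs after participants know their arm, it may already reflect their reaction to allocation and is no longer a clean pre-randomisation value.

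**Working it through.** No sample size, power or alpha figure depends on this point, so the check compares sections of the article.

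**Part 1: who knows the arm**

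1. Randomization and blinding: assessors perform the allocation, so they know the arm of each participant they allocate.
2. Outcomes (measures): assessors are the staff trained on every part of the assessment. Table 4 places the two performance tests within it at T0, T1 and T2.
3. Physical performance: the Y-Balance result is the greatest reach over three attempts per direction and leg, relative to leg length. The chair stand result is a count in 30 seconds. Both leave room for examiner influence.
4. No section names a separate rater for T1 or T2.
5. By outcome:
   - T0 performance tests: performed before allocation, so not affected.
   - T1 and T2 performance tests: exposed whenever the tester knows the arm.
   - HOOS/KOOS function and pain NRS: reported by the patient, so the assessor's knowledge matters little.

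**Part 2: where the ten days fall**

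A ten-day recording cannot fit inside one visit. Physical activity (PA) gives the wear period but not the day on which the device is handed out. Three sequences fit some or all of the text:

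| Sequence | Baseline days after allocation | Agrees with T0 preceding randomisation? |
|---|---|---|
| Device issued and worn before the t0 visit, allocation at the visit | 0 | Yes |
| Device issued at the visit, allocation held until its return | 0 | Yes, if t0 means the whole T0 stage |
| Device issued at the visit, allocation at the same visit | 10 | No, for this measure |

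The range is 0 to 10 days, and the article does not settle it.

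**Conditional consequence of Part 2**

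If knowledge of the arm shifted mean baseline activity by x between arms, and baseline activity entered the model with slope b, the adjusted effect would move by −b·x. With an assumed b of 0.5 to 0.7, that is −0.5x to −0.7x. Neither x, nor its sign, nor b is given in the document. This shows a mechanism and is not an estimate.

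**How much can still be changed**

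Trial status reports 85 enrolled by January 10, 2023 out of a target of 330, so 330 − 85 = 245 were still to come (245/330 = 74%). Enrolment opened in mid-November 2022, and T1 falls three months after the intervention starts. No T1 test was therefore due when the article was submitted.

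**The case against.** The strongest reply on Part 1 is that bias requires an arm-aware person to test the same participant 3 or 12 months later, and the article never says that the same individual does so. That is correct, and the point is limited accordingly. The article is also condensed, and silence on blinding would not by itself be a finding. The point here rests on a stated rule that gives allocation to the assessing group, with no other rater named. The training of assessors standardises the tests but does not blind anyone. It is also true that secondary outcomes are to be analysed descriptively and without Bonferroni correction, which limits the consequence.

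On Part 2, t0 can be read as a stage and not a single visit, two sections place T0 before randomisation, and the two flow figures that might show the sequence are not in the copy at hand. This reply largely stands.

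A reader might infer three stronger claims that the document does not support:

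- **That baseline accelerometry definitely follows allocation.** This holds only if the device is handed out at the visit where allocation takes place, which is not stated.
- **That the physical activity effect is biased downward by a known amount.** The covariates named for the primary analysis are baseline pain and function. Adjustment for the respective baseline value is mentioned only in the sample size section, and secondary outcomes receive unspecified regression models. Size and direction are both unknown.
- **That concealment is broken.** Allocation through REDCap after the initial assessment does not in itself reveal the next assignment.

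**Conclusion.** The concern holds in a limited form. The stated rule gives knowledge of the arm to the staff group that runs the Y-Balance and chair stand tests, and no arm-unaware tester is provided for T1 and T2. Results of these two secondary outcomes at both follow-ups are open to detection bias of unknown size. This assumes that at least some participants are tested at follow-up by someone who knows their arm, which is a fair reading of the article but is not stated in it.

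For accelerometry, the sections on allocation and on T0 are not reconciled for a measure that takes ten days. The baseline may be recorded after allocation is known, for anything from 0 to 10 days.

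The primary comparison and the T0 performance tests are little affected. The point is worth acting on because the change is cheap and most allocations were still to come at submission, but it does not threaten the main conclusion.

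**What to change.** 1. Separate allocation from follow-up testing. Preferably, study or data-centre staff who do not test participants release the allocation in REDCap. The article does not confirm that each centre has such a person. The minimum is therefore to roster a different, arm-unaware assessor for that participant's T1 and T2 performance tests.
2. Ask participants not to disclose their arm to the tester.
3. State that allocation is released only once all T0 measures are complete, including return of the accelerometer and diary, and bring the wording of Randomization and blinding into line with Table 1 and Participant timeline.
4. For participants already enrolled, compare recording dates with the allocation date. Do not use as a baseline covariate any accelerometry recorded after allocation.
5. If arm-unaware testing is not feasible, report the performance tests as assessed unblinded.

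The cost is a change of REDCap rights or of the rota, a short procedure note and some scheduling effort. If the device is handed out at the visit, allocation comes about two weeks later (ten days of wear plus an assumed few days for return). Some participants will still reveal their arm, so blinding of the testers will be incomplete.

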#### Data collection and management

The Competence Centre for Clinical Trials Bremen (KKSB) links data from different sources for the summative, the health economic and the process evaluation (data acquired during baseline and follow-up assessments, routine data from TK, and app-based data). In the assessments, we use machine-readable paper documents, pseudonymized in the Trust Centre at the KKSB and forwarded to the data management department of the KKSB for conducting the summative evaluation following checks for missing data and plausibility to ensure data quality.

#### Data protection

In accordance with data protection legislation, the Trust Centre of the KKSB destroys the key at the earliest possible time when no further requests are open. Data access is exclusively granted to authorized employees of the KKSB involved in this project. All study data is stored in a secured network. A joint controller agreement regulates joint responsibilities among the consortium partners in the processing of personal data pursuant to article 26 General Data Protection Regulation (GDPR).

#### Statistical analysis

The primary outcomes comprising physical functioning (HOOS/KOOS) and pain reduction (NRS) at 12 months from baseline are compared between the intervention and control group using Bonferroni-adjusted analysis of covariance with gender, index joint, allocation (individual/group treatment), baseline values (pain and physical functioning) and the study centre as covariates. In sub-group analyses, corresponding models will be applied only to patients with hip or knee OA and only to women or men, respectively. Wherever required, differences in the effects are tested by expanding the overall model with corresponding interaction terms. Study centre effects are studied in a similar way. A secondary analysis will examine intervention group differences in the time course of pain and physical functioning, including all assessment appointments and using mixed models. Effects on the secondary outcomes are investigated descriptively (and without Bonferroni correction) using appropriate regression models. The analysis is primarily based on the *intention-to-treat* principle. Missing values will be considered by multiple imputation and *maximum likelihood* principle, respectively. If large numbers of imputations will be necessary, a robustness analysis with alternative imputation strategies will be carried out. All statistical analyses are defined in a Statistical Analysis Plan prior to the completion of patient recruitment.

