4. What: Procedures	The SmArt-E intervention is divided into an in-person phase and a self-training phase. If more than four persons are interested in participating at the same time, the intervention can take place in a group setting, otherwise it is conducted in individual physiotherapy sessions. Each session consists of an educational and exercise part. The first session is also about getting to know the app and its functions. During the self-training phase, the participants continue the intervention with the support of the mobile phone app. In case of questions or problems, it is possible to contact the physiotherapist via the chat function of the app. Six months after the start of the intervention, refresher sessions will take place to repeat specific educational content. If necessary, additional individual physiotherapy can be delivered.
5. Who provided	Trained physiotherapists perform the in-person exercise programme and education as well as the refresher sessions. Physiotherapists receive 2 days (4 hours each) of training specific to the SmArt-E intervention from skilled members of the study team. Individual therapy (if required) can be delivered by any physiotherapists without special training.
6. How	During the in-person phase, the intervention is provided in either individual (one-to-one) or group setting (4–8 participants). After the in-person phase, SmArt-E also includes the phase of self-training planned from the distance with the support of a mobile phone app and with remote physiotherapeutic support using the app’s chat feature.
7. Where	Three study centres: Bochum/Dortmund/Essen (North Rhine-Westphalia, Germany), Cottbus/Senftenberg (Brandenburg, Germany), Tübingen/Reutlingen (Baden-Württemberg, Germany) The in-person sessions are delivered in an outpatient physiotherapy setting. During the self-training phase, participants decide themselves where to exercise, probably in their own homes. Individual physiotherapy and refresher sessions will also take place in the respective physiotherapy practice.

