#### Sample size

We aim to recruit 330 patients, equally distributed among the intervention and control group. The sample size calculation assumes an effect size of Cohen’s *d* = 0.34 for the comparison of the *SmArt-E* intervention and usual care for the primary outcomes of pain and physical functioning after 12 months. This assumption is derived from a recent meta-analysis involving 44 clinical studies evaluating internationally established, comparable exercise therapy compared to *do-nothing* or *sham* control conditions and a dropout rate of 15%, resulting in effect sizes of *d* = 0.49 for pain and *d* = 0.52 for physical functioning [23]. A comparable RCT with digital support demonstrate similar results, in which the authors find a greater pain reduction of approximately − 1.0 (±2.3) points on a 11-point NRS in the intervention group compared with the control group, corresponding to an effect size of *d* = 0.44 [33]. Regarding physical functioning, an effect of *d* = 0.66 is observed. We assume smaller effect sizes for the SmArt-E intervention as this will be compared to current usual care, which should be more effective than *Do-Nothing* or *Sham*. Based on a *t*-test for independent samples, one-sided *α* = 0.05 and *β* = 0.80, a sample size of *n* = 274 is necessary when considering the number of outcomes and Bonferroni corrections (*n* = 137 per group). Target sample size is increased to *n* = 330 to compensate for dropouts of up to 20%. Additional power is gained by statistically accounting for age, gender, and the baseline value of the respective outcome.

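### The sample size and primary ANCOVA make no allowance for the nesting of intervention patients in practices, therapists and training groups; if outcomes correlate within these, the standard error is too small

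*Protocol article*

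**What the plan says.** All references are to the protocol article.

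- **Delivery.** Table 3 (TIDieR), item 6, says that in the in-person phase "the intervention is provided in either individual (one-to-one) or group setting (4–8 participants"). Item 5 assigns the in-person programme and the refreshers to physiotherapists trained for the trial. Under Randomization and blinding: "Participants of the intervention group will be treated in the nearest participating physiotherapy practice".
- **Continuing contact.** Under Content of the intervention and SmArt-E app, the supervising physiotherapist can adapt the programme and supports the patient by chat and video.
- **Sample size.** The calculation rests on a t-"one-sided *α* = 0.05 and *β* = 0.80"-type specification only in part: the test is a t-"test for independent samples", the error settings are "one-sided *α* = 0.05 and *β* = 0.80" (the 0.80 is evidently power), and the total of 274 is reached "when considering the number of outcomes and Bonferroni corrections". No ICC or design effect appears.
- **Primary analysis.** Under Statistical analysis, the outcomes "are compared between the intervention and control group using Bonferroni-adjusted analysis of covariance". The covariates are gender, index joint, individual or group format, baseline values and study centre. Mixed models are named only for the secondary analysis of the time course.

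**The concern.** Patients who share a therapist, a practice or a training group may have more similar 12-month outcomes than patients who do not. Here that sharing is created by the trial treatment, so it arises mainly in the intervention arm (a partially nested design). An ordinary ANCOVA assumes independent residuals. Study centre has only three levels and treatment format only distinguishes individual from group delivery, so neither term absorbs correlation within practices, therapists or groups.

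If such correlation exists, the variance of the intervention-arm mean is understated. The confidence interval is then too narrow and the per-outcome error rate rises above its nominal level. An analysis that corrects for this would need more patients for the same power.

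**Working it through.** **Inputs from the Sample size section.** "The sample size calculation assumes an effect size of Cohen’s *d* = 0.34", a one-sided alpha of 0.05, Bonferroni over two primary outcomes (0.05/2 = 0.025 one-sided per outcome), power 0.80, equal arms.

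**Reproducing the plan's figure.** Exact noncentral-t power for two independent samples with d = 0.34 and one-sided 0.025 first reaches 0.80 at 137 per group, or 274 in total. This matches the article exactly, so the figure contains no allowance for clustering. The normal approximation used below gives:

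δ = 0.34 × √(137/2) = 2.814; power = Φ(2.814 − 1.960) = 0.803.

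**Assumptions, not in the documents.** ICC 0.01 to 0.10 in the intervention arm; every intervention patient in a cluster of m = 6 (the middle of the 4 to 8 range); controls independent.

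**Formulas.** The intervention-arm variance is multiplied by 1 + (m − 1) × ICC and the control-arm variance is unchanged. For equal arms, the variance of the difference is multiplied by

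V = 1 + (m − 1) × ICC / 2.

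- Error of the planned (uncorrected) test: 1 − Φ(1.960/√V)
- Power of the planned test: Φ((2.814 − 1.960)/√V)
- Power of a cluster-corrected test: Φ(2.814/√V − 1.960)

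**Example, ICC 0.05.** V = 1 + 5 × 0.05/2 = 1.125 and √V = 1.061. Error = 1 − Φ(1.848) = 0.032. Planned-test power = Φ(0.805) = 0.79. Corrected-test power = Φ(2.653 − 1.960) = 0.756.

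| ICC (m = 6) | V | One-sided error, planned test | Power, planned test | Power, corrected test |
|---|---|---|---|---|
| 0.01 | 1.025 | 0.026 | 0.80 | 0.79 |
| 0.02 | 1.050 | 0.028 | 0.80 | 0.78 |
| 0.05 | 1.125 | 0.032 | 0.79 | 0.76 |
| 0.10 | 1.250 | 0.040 | 0.78 | 0.71 |

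The error column and the last column belong to different analyses. The planned test has the raised error and nearly its nominal power; the corrected test restores the error and pays in power.

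**Sensitivity to cluster size.** Over ICC 0.01 to 0.10, the planned test's error is 0.026 to 0.034 for m = 4 and 0.027 to 0.046 for m = 8.

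**Effect of baseline adjustment.** The Sample size section expects extra power from covariates. If the baseline-outcome correlation is ρ (assumed) and the ICC applies to residuals, δ is divided by √(1 − ρ²). At m = 6 and ICC 0.05, corrected power is 0.79 for ρ = 0.3 (δ = 2.950) and 0.865 for ρ = 0.5 (δ = 3.249). At ICC 0.10 and ρ = 0.5 it is 0.83. The error column does not change, because adjustment for patient covariates does not correct a standard error for clustering.

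**The case against.** **Clustering may be slight at 12 months.** In-person contact lasts 6 to 12 weeks, after which patients train at home with the app apart from refreshers and contact on demand. Training parameters have defaults, and education and therapist training are standardised. This stands: it is a good reason to expect a low ICC, and at 0.01 the effect is negligible. It is not a reason to fix the ICC at zero.

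**Cluster sizes are uncertain.** Group delivery is optional, so group-level correlation touches only part of the arm. The three planned focus groups of ten physiotherapists suggest about 30 therapists, though this is not a stated count. That would give 137/30 ≈ 4.6 analysed patients each, and an error of 0.027 at ICC 0.02 or 0.030 at ICC 0.05. Practice clusters could be larger, but no figure supports a size. Practice and therapist nesting still applies to the whole arm.

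**Some controls may be clustered too.** Usual care can include physiotherapy. Treating controls as singletons is a simplification.

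**The analysis plan may deal with it.** The article promises a separate plan, which is not shown and could add a cluster term. But the article itself names the primary model and the sample-size test, and as written both assume independence.

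**A stronger reading is tempting:** that the error rate is certainly exceeded and that the trial lacks its 80% power. The documents support neither. The first needs an ICC above zero, which they do not give. The second confuses the corrected test with the planned one and ignores the gain from baseline adjustment.

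**Conclusion.** The mismatch between design and analysis is established: intervention patients are nested in practices and therapists, and partly in groups, while both the sample size and the primary ANCOVA treat all patients as independent. The consequence is conditional. If the intervention-arm ICC is above zero, the planned test is anti-conservative. For clusters of 6 this ranges from trivial (0.026 at ICC 0.01) to material (0.040 at ICC 0.10), against 0.025.

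Correcting for it would lower power at 137 per group to between 79% and 71% over the same range before covariate adjustment. Whether any net loss remains after adjustment depends on a baseline-outcome correlation that the article does not state. A reader might also infer that practice, therapist or group identifiers are not being collected; the article does not say so. The point merits a change to the plan but does not call the design into question.

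**What to change.** - Keep the same fixed effects and add to the primary model a random intercept for one prespecified treatment cluster (therapist or practice; training group where used) in the intervention arm only. Treat controls as singletons and use small-sample degrees of freedom.
- Prespecify a fallback of small-sample cluster-robust standard errors for the case where the cluster variance is estimated at its boundary, which is a real possibility with many small clusters.
- Make sure that the cluster identifier is in the analysis data.
- State that the 80% power assumes no clustering, and give power over a stated range of ICC and cluster size, with and without an assumed gain from baseline adjustment.

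The cost is a model change in the analysis plan and one identifier per intervention patient. The downside is slightly wider intervals and a less favourable power statement. Treatment, eligibility and randomisation are untouched.
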